## Abstract

**Background:**

Pediatric acute gastroenteritis (AGE) is a common childhood illness with substantial health, family, and system impacts. Connecting parents to evidence-based patient education is key to effective decision-making and therapeutic management of AGE. Digital knowledge translation (KT) tools offer a promising approach to communicate complex health information to parents; therefore, we developed a whiteboard animation video for parents about AGE. To optimize future effectiveness evaluation of this video, the purpose of this pilot study is to assess feasibility of effectiveness outcomes and specific trial methods in four key trial domains.

**Methods:**

A single-site, parallel-arm, pilot randomized trial will be conducted. The trial will employ quantitative and qualitative methods to evaluate feasibility objectives in key scientific, process, management, and resource domains. Parents seeking care for a child with AGE in the emergency department (ED) over a 6-month period will be randomized to receive the whiteboard animation video or a sham control video. Quantitative data will be collected electronically in the ED and at home (4–10 days post-ED visit). Qualitative data will be collected via semi-structured interviews with experimental condition participants after quantitative data collection. Data will be collected to perform a sample size calculation for a full-scale trial. Scientific outcomes will include parental knowledge, decision regret, and health utilization, and estimation for these outcomes will use confidence intervals (CI) of different widths to illustrate strength of preliminary evidence. CIs will be presented alongside minimum clinically important differences (MCIDs) calculated using two methods: (1) data driven and (2) patient perspective. Descriptive statistics will be calculated to describe process, management, and resource domain outcomes. Qualitative thematic analysis will be conducted to describe additional process, management, and resource outcomes in the experimental group. Analyses will be performed using intention-to-treat.

**Discussion:**

This pilot randomized trial will inform the design and conduct of a full-scale, effectiveness trial by gathering key data in four domains: scientific, process, management, and resource. These results will impact the emerging field of KT efforts targeting health consumers and advance the science on the best mode of patient education for acute childhood illnesses.

**Trial registration:**

clinicaltrails.gov registration number NCT03234777. Registered 31 July 2017.

**Electronic supplementary material:**

The online version of this article (10.1186/s40814-018-0318-0) contains supplementary material, which is available to authorized users.

## Background

Pediatric acute gastroenteritis (AGE), characterized by vomiting and diarrhea, is a common presentation in emergency departments (EDs) and remains a leading cause of global pediatric morbidity [1–4]. In Canada and other developed countries, AGE is most often caused by viruses [1]. Annually, there are five million cases of pediatric AGE in Canada and it represents 10% of Canadian pediatric ED visits, resulting in a yearly healthcare cost of $3.7 billion [5]. In addition to substantial health system impacts, pediatric AGE affects families in a multitude of ways, including negative effects on physical and emotional wellbeing of children and parents [6] and frequent parental work loss [7].

A recent Canadian, qualitative study of parents/caregivers (*n* = 15) highlighted the “real-life” complexity that influences health decision-making for pediatric AGE (i.e., past experiences and life circumstances) as well as AGE-related information needs, which included symptom management, understanding the normal course of illness, the cause of illness, information specific to dehydration, where to purchase helpful items, and how to talk to their child about AGE [8]. An American, cross-sectional study that evaluated parent/caregiver (*n* = 229) knowledge about AGE indicated a wide variation in knowledge levels and demonstrated that knowledge was positively correlated to accessibility of health information, level of education, ethnicity, and experience with dehydration. This study recommended that future education interventions should be designed to improve general knowledge [9]. A Canadian non-randomized trial targeting parents/caregivers (*n* = 105) of children with AGE in the ED evaluated one-on-one nursing education session in the ED and an educational home visit versus no intervention control. The study found a small (not statistically significant) increase in knowledge at 1 month, but this change was not sustained at 6 months [10]. A French cluster randomized trial targeting adults and parents/caregivers (*n* = 400) with children with either tonsillitis or AGE evaluated the effect of patient information sheets. This study found statistically significant, positive effects on behavior (primary) and knowledge (secondary) outcomes in the information sheet child sub-group compared to the no information, control child sub-group 10–15 days post-intervention [11].

Knowledge translation (KT) is defined as the synthesis, exchange, and application of knowledge to improve the health of individuals, provide more effective health services and products, and strengthen health care systems [12]. Current approaches to KT research are largely focused on aligning the behaviors of health professionals with best research evidence; however, there are increasing calls for KT interventions for health consumers to influence health knowledge, decision-making, and service utilization [13], especially given the many alternative health options open to parents through the Internet. At present, there is little guidance on the most effective approach, content, duration, and intensity of education for this diverse population [14–16]; however, it is hypothesized that providing evidence-based child health information to parents and families has the power to ensure consistent parental management of child health over time and across settings [17], increase effective health decision-making [18], and reduce health system costs [18]. It is critical to generate empiric evidence to help determine the optimal modes for delivering evidence-based information to parents and families.

At present, it is routine practice to provide health education to parents seeking care for their children in EDs to guide care after discharge [17]. Typically, education is provided at the end of the emergency department visit when parents are tired and anxious to leave, making them less likely to ask important questions and retain information [19]. Additionally, information provided verbally is often brief [20] and written information is often too complex for most adults to comprehend [21, 22].

Since online tools (e.g., podcasts, e-books, animations, and infographics) are low or no cost, easily accessible, and can be consumed on demand, they hold promise as an effective approach to KT for parents and caregivers seeking research-based information related to child health [23, 24]. Additionally, online platforms allow content to be viewed as frequently as needed, which may improve information retention and compliance [24].

To address the research-practice gap in pediatric AGE and provide parents with a reliable, research-based information resource, our research team developed a 3-min whiteboard animation video using patient-oriented research methods [25]. Whiteboard animation videos are short, hand-drawn, and narrated videos optimized for online streaming. Video content was drawn from knowledge synthesis results of treatment and management strategies for pediatric AGE [1]. The video storyline was developed from a qualitative study (*n* = 15) that gathered and synthesized stories from parents/caregivers of children with vomiting and diarrhea who visited an ED for healthcare [8]. Video prototypes were reviewed, and a final version approved by pediatric emergency clinicians, research nurses, and parents. The video depicts a family with a sick child trying to determine whether medical attention is required. The family recalls an information sheet given to them at a hospital when their child was ill with the same symptoms at an earlier time. The family assesses their child using the information sheet and determines to monitor and manage the child’s illness at home until symptoms resolve. The family describes worsening symptoms that would require them to take their child to the emergency department. Artists, including a script writer, animators, and voice actor, were contracted to work with the research team to ensure high-quality video production.

Rigorous evaluation of the effectiveness of the whiteboard animation video is a critical next step. Given some uncertainty regarding the most appropriate methods for evaluating the effectiveness of KT tools for parents [26], including best outcome measures and parameters for sample size calculations, we have chosen to first undertake a pilot trial [27–29]. We are also interested in exploring the feasibility of using an electronic platform to assist with recruitment, intervention delivery, and data collection. The study objectives are listed in Table 1 according to four key pilot trial domains [27].

**Table 1 Tab1:** Study objectives

Pilot trial domains	Study objectives
Scientific domain	• To estimate the potential effectiveness of a digital knowledge translation tool for parents/caregivers about pediatric AGE. Effectiveness outcomes include knowledge, decision regret, and post-ED healthcare utilization.
	• To identify the perceived benefit and value of KT tools for this population, including important components that enhance knowledge about childhood AGE and decision-making regarding choice to take child with AGE to the ED.
Process domain	• To identify whether using an electronic, web-based platform for intervention delivery and data collection is feasible with this population.
Management domain	• To describe this population’s willingness to participate in future, similar research (i.e., full-scale trial).
Resource domain	• To estimate time required for participants to complete data collection forms.
	• To identify whether using iPads to collect data is feasible with this population.

## Methods

This is a parallel-arm, randomized, pilot trial. Convenience sampling will be used to recruit parents/caregivers seeking care for a child with vomiting and diarrhea in the ED and randomize them to receive the intervention of interest (i.e., whiteboard animation video) or a sham control condition (i.e., standard video of similar length). Data will be collected using quantitative and qualitative methods over a 6-month period. This protocol has been registered on clinicaltrails.gov (NCT03234777) and has obtained ethics approval from the University of Alberta Health Research Ethics Board and operational approval from the provincial health authority.

### Study location and population

The study will be conducted at one Canadian, tertiary care, pediatric hospital. Parents meeting the eligibility criteria in Table 2 will be invited to participate.

**Table 2 Tab2:** Study eligibility criteria

Study eligibility criteria	
Inclusion criteria	1. Parent or caregiver of a child 16 years old or younger.
	2. Child is presenting to the ED with vomiting and diarrhea.
	3. Parent is fluent in English.
	4. Parent is willing to be contacted for follow-up data collection.
Exclusion criteria	1. Child has significant chronic gastrointestinal problem or inflammatory bowel disease (i.e., Crohn’s disease, inflammatory bowel disease, ulcerative colitis, chronic constipation).
	2. Child is taking immunosuppressive therapy or known history of immunodeficiency.
	3. Child has undergone oral or gastrointestinal surgery within the preceding 7 days.
	4. Child has had a prior visit to the ED for vomiting and diarrhea within the preceding 14 days.

### Recruitment

ED triage records will be screened in real time to identify potential study participants. The parent/caregiver of consecutive individuals with primary complaint of vomiting and diarrhea will be approached in the ED waiting room post-triage assessment (Fig. 1) during data collection recruitment hours (0900–2300 Monday to Friday, 1500–2300 Saturday and Sunday). A member of the study team will assess inclusion/exclusion criteria and review the study information letter. Informed consent will be indicated on iPads as part of the electronic data collection platform.

**Fig. 1 Fig1:**
[figure not shown]
Trial flow and timing of data collection

### Interventions

The interventions take place in the ED waiting room post-triage assessment and prior to consultation with a physician. Post-intervention, all participants will receive standard medical care from healthcare providers. The study hospital has an information sheet about AGE; however, education about AGE including whether the information sheet is given to parents/patients is at the discretion of the attending physician.

For this study, the experimental intervention is a 3-min, whiteboard animation video about a family’s experience with pediatric AGE (URL: https://www.youtube.com/watch?v=5N3gMtvkCqk&list=PLxWz0fEGuv6o5LrEpvdsmQFs5zB1dIFR8&t=17s&index=12). The sham control condition is a 3-min standard video developed by the Centres for Disease Control and Prevention about hand washing for infection control (URL: https://www.cdc.gov/cdctv/healthyliving/hygiene/fight-germs-wash-hands.html) [30]*.* Parents will view either the experimental or sham control intervention once on an iPad in the ED waiting room post-triage assessment. Disposable headphones will be provided with the iPads to maintain blinding. At the end of data collection in the ED (post-intervention questionnaire 1), parents can opt to receive a link to their assigned video via email to view as often as they wish from their own device(s). Parents from the experimental intervention group that are participating in the qualitative interview will view the whiteboard animation video again at the start of the interview.

### Randomization

Blocked randomization with randomly chosen block sizes will be used to ensure equal distribution of participants to the experimental and sham intervention study arms [31]. The blocked randomization sequence will be computer generated. Following sequence generation, the randomization sequence will be entered into a confidential module on the electronic platform. Once the sequence is entered, the randomization module will only be accessible using a confidential password. The randomization sequence will be kept confidential. It will be inaccessible to data collectors/outcome assessors and to the study participants.

After completing the pre-intervention questionnaire, including demographic information and baseline outcome data, on the electronic data collection platform, individual parents/caregivers will automatically be randomized to one of the study conditions (i.e., experimental intervention or sham control) based on the randomization sequence. This process will be seamless to participants. After viewing the study condition materials, participants will be automatically directed to post-intervention questionnaire 1. At study completion, all participants will receive a thank you email with links to both videos shown in the study.

### Blinding

Using an electronic platform for data collection, study group allocation, and intervention viewing will allow participants to access the interventions and provide data independent of the research team. Participants and study staff will be blind to how the content on the iPads differs between groups during data collection.

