### Data collection

Participants will be provided with disposable headphones and an iPad containing the iCare Adventure electronic platform. iCare Adventure is a client-server based e-therapeutics platform designed to expedite and improve the management of patients’ care within pediatric ED facilities. iPads, which are locked to the iCare Adventure app, are given to parents participating in research in the ED. All content within the app, including screen flow, textual content, images, videos, protocols, and questionnaires, is controlled on a centralized server. When the application restarts, it calls to the server, the iPads report all user interactions back to the server in real time, and the server can dynamically create real-time reports of the aggregated data. Data collection processes and forms will be piloted with the research team prior to the start of data collection.

The informed consent process and quantitative data collection will be completed on iCare Adventure, and participants will be automatically given the questionnaires and appropriate intervention (i.e., whiteboard video or sham video) based on the randomization sequence. A unique study identifier will be generated for each participant within the iCare Adventure platform. All data collection points will be electronically time-stamped.

As part of the post-intervention questionnaire 1, participants receiving the experimental intervention will be asked about their willingness to be contacted later for an individual, in-depth, semi-structured, qualitative interview. If interested, they will provide contact information (i.e., name, phone number, and best time to contact) and a member of the research team will follow up via telephone.

Using a qualitative descriptive approach [37, 38], a semi-structured interview guide will be used. This data collection strategy will be used to obtain all information required, probe participants’ responses, and give participants freedom to respond and illustrate concepts in an open-ended fashion [36]. Interview questions will move from the general to the specific, with interviews later in the data collection period becoming increasingly more focused [39]. Interviews will be conducted in-person or over the telephone and will be audio recorded. Audio recordings will be anonymized, de-identified, and transcribed verbatim by a third party contractor. Transcriptionists will sign a confidentiality agreement.

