The following data will be collected over the course of this study:Pre-intervention questionnaire (baseline, see Additional file 1): Participants will complete a pre-intervention questionnaire that includes demographics, knowledge questionnaire, and Decision Regret Scale within the iCare Adventure platform on the iPad.**Participants will then be randomized to view the study intervention or the standard care intervention within the iCare Adventure platform on the iPad. This process will be seamless for the participants.Post-intervention questionnaire 1 (immediate, see Additional file 2): After viewing the intervention, participants will complete the knowledge questionnaire and Decision Regret Scale a second time. In addition, participants will complete two items assessing their own performance on the knowledge questionnaire and Decision Regret Scale and one item regarding the perceived value and benefit of the KT tool. They will also be asked if they would like a video link emailed to them. At the end of this questionnaire, parents will be informed that the post-intervention questionnaire 2 will be emailed to them 4 days after this ED visit for completion at their earliest convenience. Experimental intervention group parents will be asked about participation in a qualitative focus group at this time.Post-intervention questionnaire 2 (4–14 days post-ED, see Additional file 3): Participants will be emailed a secure link on day 4 post-ED discharge to complete the knowledge questionnaire and Decision Regret Scale a third time, two items assessing their own performance on the knowledge questionnaire and Decision Regret Scale, three items related to healthcare utilization, and three items related to the perceived value and benefit of the KT tool (if applicable). Reminders to complete post-intervention questionnaire 2 will be sent to those who have not completed the survey every third day (day 7, 10, 13) to complete the survey by day 14 post ED-discharge. Previous research has demonstrated that 82% of AGE cases are resolved in 3 days or less and 14 days [40] represents the outer limit for pediatric AGE resolution [41].Post-intervention semi-structured interview (sub-sample of experimental group, see Additional file 4): Participants in the experimental group indicating willingness to participate in an in-depth, semi-structured, qualitative interview will be contacted via telephone after completion of post-intervention questionnaire 2. Up to three phone calls will be made to establish interview date/time. Qualitative interviews will focus on satisfaction with iCare Adventure platform, perceived benefit and value of the KT intervention, and willingness to participate in future, similar research.

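### Only experimental-arm parents are invited to interview before questionnaire 2, which may alter its completion in one arm, and the interview procedure conflicts with the unqualified statement that staff are blind

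*Protocol article*

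**What the plan says.** The Blinding section states: "Participants and study staff will be blind to how the content on the iPads differs between groups during data collection". It explains that the electronic platform "will allow participants to access the interventions and provide data independent of the research team". The Randomization section adds that data collectors and outcome assessors cannot reach the sequence.

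The Data collection section describes the interview invitation twice. The running text reads: "As part of the post-intervention questionnaire 1, participants receiving the experimental intervention will be asked about their willingness to be contacted later". Those interested leave their name, a telephone number and a suitable time to call. The list of questionnaires repeats the restriction to one arm: "Experimental intervention group parents will be asked about participation in a qualitative focus group at this time". (It says focus group here and individual interview elsewhere.) No matching question to control parents is described.

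For questionnaire 2, "Participants will be emailed a secure link on day 4 post-ED discharge". Reminders go to every non-responder on days 7, 10 and 13. Experimental-arm parents who are willing to be interviewed "will be contacted via telephone after completion of post-intervention questionnaire 2". Under Interventions, the whiteboard video is played again at the start of the interview.

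**The concern.** In a two-arm comparison of videos, the arms should be handled alike apart from the video until the last outcome is collected. Here one arm also receives a request for further involvement, and its volunteers hand over contact details, before the time 3 data exist. Two things are at stake.

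The first is completion of questionnaire 2. Drop-out at that point is a listed process outcome (Table 3), and the pilot is meant to inform a full-scale trial. The time 2 to time 3 change (Data analysis) can be formed only for parents who return questionnaire 2. If the invitation alters who returns it in one arm, randomization no longer secures comparability among those parents.

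The second is the staff-blinding sentence. Every name on the volunteer list belongs to the experimental arm, and an interviewer sees the experimental video. The sentence makes no exception for these staff.

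**Working it through.** The protocol gives no sample size, expected drop-out or acceptance rate, so there is no stated figure to reproduce. The check is a reading of the sequence, followed by an illustration on assumed inputs.

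**Sequence for one parent**
1. In the ED: baseline questionnaire, randomization, video, questionnaire 1. Experimental arm only: interview question and contact details.
2. Day 4 after discharge: questionnaire 2 link to both arms, with the same reminders.
3. After questionnaire 2: telephone call to experimental-arm volunteers, then the interview.

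The interview itself cannot influence that parent's time 3 answers. The invitation comes before them and could influence whether they are given.

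**Shift in completion (assumed inputs)**
Arm difference = acceptance × change in return among acceptors.
- Low: 0.30 × 0.10 = 0.03, or 3 points.
- High: 0.50 × 0.20 = 0.10, or 10 points.
- Under equal allocation the pooled completion figure moves by half of this, 1.5 to 5 points.

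These figures assume a non-zero effect; zero or a fall is also possible.

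A second illustration uses the 12–20 interviews in the Sample size section. If all those interviewed would otherwise have been lost, the shift is interviewees ÷ arm size:

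| Assumed parents per arm | 12 interviewees | 20 interviewees |
|---|---|---|
| 50 | 24 points | 40 points |
| 100 | 12 points | 20 points |
| 150 | 8 points | 13.3 points |
| 250 | 4.8 points | 8 points |

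This is an extreme case for those interviewed. It is not a bound for the arm, because every experimental parent is asked. The 250 row would require enrolling all of the roughly 500 presentations, which the protocol does not claim.

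**Effect on the time 3 knowledge comparison (assumed inputs)**
Let d be the mean of completers minus the mean of non-completers, equal in both arms. Completers in an arm with completion p overstate that arm's mean by d(1 − p). The bias in the arm difference is therefore d(1 − p_exp) − d(1 − p_ctrl) = −d(p_exp − p_ctrl).
- d = 0.5, gap 0.05: size 0.025 points.
- d = 2, gap 0.20: size 0.4 points on the 0–8 scale.

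**Would a gap be noticed?**
Take 60% against 70% completion, two-sided 5%, normal approximation. Power = Φ{[0.10 − 1.96 √(2 × 0.65 × 0.35 / n)] / √[(0.60 × 0.40 + 0.70 × 0.30) / n]}. This gives about 18% at n = 50 per arm, 32% at 100, 44% at 150 and 65% at 250. A 10-point gap could easily pass unremarked.

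**Staff blinding**
The invitation rule and the interview procedure, set beside the Blinding sentence, leave two exposures. Staff who see the volunteer list learn the allocation of those on it. Interviewers learn what the experimental video contains. Each interview follows that parent's own questionnaire 2, but other parents may still be in recruitment or follow-up. The protocol does not hold interviews back until these end, and it describes the thematic analysis as concurrent with data collection. The sentence therefore cannot be true of these staff as written.

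**The case against.** A reader might infer that the invitation unblinds parents by telling them that theirs is the video under study. The text does not support this. Each parent sees one iPad, and nothing shows that parents are told the other arm is not asked. In the Data collection section, questionnaire 1 puts a perceived-value item and the offer of a video link to all participants, so control parents are also treated as having viewed a studied tool.

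A reader might also infer that the invitation raises retention. That would be most plausible if parents knew the interview follows questionnaire 2, but the protocol describes only the order of study procedures, not what parents are told. It states no interview incentive. Every enrolled parent has already agreed to follow-up contact (Table 2), which leaves less room for an uplift, and volunteers may be those who would have responded anyway. This stands: direction and size are unknown.

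Finally, even staff who know allocation have little route to time 3 results. Answers are self-entered, the reminder schedule is uniform, and volunteers are telephoned only afterwards. Rules on who sees the contact list may sit in a fuller document. This also stands, and it limits the consequence of the staff exposure. It does not remove the one-arm procedure, which the article states twice, or make the blinding sentence accurate for interviewers.

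**Conclusion.** The point holds in a limited form and is minor. The invitation is an avoidable difference between arms, placed before a declared drop-out outcome and the sustained change score. Its effect on questionnaire 2 completion is plausible but unquantified. The 3–10 point difference between arms and the 0.025–0.4 point bias in knowledge rest wholly on assumed inputs. No figure in the protocol is shown to be wrong.

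On blinding, the conflict concerns staff who handle the volunteer list or conduct interviews. The documents do not show that participants are unblinded, nor that staff knowledge would change time 3 data.

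**What to change.** 1. Move the interview invitation and the contact fields to the last screen of questionnaire 2, after all outcome items, shown to the experimental arm as now. Alternatively, keep them in questionnaire 1 and put the same contact question to both arms.
2. Report questionnaire 2 completion by arm as well as overall.
3. Limit the blinding sentence to participants and to staff not involved in the interviews, and keep the volunteer list from recruiting and follow-up staff. Moving the invitation does not achieve this by itself, because interviewers still see the experimental video.
4. Use one term, interview or focus group, throughout.

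The cost is a change of screen order, an access rule and a few sentences. Willingness would be asked online after discharge instead of in the ED, so slightly fewer parents may volunteer. Only 12–20 interviews are sought, and volunteers are already telephoned only after questionnaire 2, so the loss should be small. Under the alternative, control parents would leave details that the present interview plan does not use, and the wording of the question would have to allow for that.
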